### Who will take informed consent? {26a}

During consultation or during dialysis, the nephrologist or (research) nurse will inform eligible patients about the study, answer questions, and invite patients to participate in the study. Patients will receive the patient information form, a folder about the study, and the informed consent form. Patients consenting in participation will hand in their signed informed consent form for the screening questionnaires at the hospital/dialysis center or return them by mail using the pre-stamped return envelope. After completing the screening questionnaires, patients who show adjustment problems—as indicated by the screening questionnaires—are invited to participate in the RCT. To participate in this part of the study, patients sign another informed consent form and return it by mail (see Fig. 1 for the participant timeline).

### Additional consent provisions for collection and use of participant data and biological specimens {26b}

Not applicable, this trial does not have biological specimens.

## Interventions

### Explanation for the choice of comparators {6b}

Participants will be randomly assigned to one of the two groups: (1) the control group that will receive care as usual or (2) the intervention group that will receive 3–4 months of ICBT treatment in addition to usual care. In the Netherlands, usual care for dialysis patients is based on a multidisciplinary approach by a team consisting of nephrologists, dialysis nurses, and specialized social workers that uses complaints and disease-specific PROMS (patient-reported outcome measures) as a base for guidance for medical and psychosocial problems experienced by individual patients. Specialized social workers have to work according to the Dutch Quality Standard for social workers on a dialysis unit. When deemed necessary, additional consultation by a medical psychologist or psychiatrist is routinely available in all Dutch dialysis centers. More information on the Dutch guidelines on renal replacement therapy can be found at https://www.nefrovisie.nl/richtlijnen-indicatoren/.

### Intervention description {11a}

#### Procedure E-HELD intervention

Participants allocated to the intervention condition will receive tailored ICBT. The ICBT intervention is guided by a trained psychologist, referred to as the “e-Coach.” All e-Coaches participating in this study have a master’s degree in health or clinical psychology and are supervised by a senior clinical psychologist with post-academic training in CBT. Treatment starts with a face-to-face intake meeting with the e-Coach. When a face-to-face meeting is not possible, the e-Coach will schedule a digital, videoconferencing meeting instead. During the intake, the patient will receive feedback on the screening results using the Personal Profile Chart in which the results are visualized. Based on the discussion of patient’s results, the patient and the e-Coach will determine patient’s top priorities for improvement and formulate treatment goals. Subsequently, the e-Coach will tailor the intervention so that it meets the patient’s needs. In addition, the e-Coach will explain the online environment and explores the patient’s wishes with regard to the intensity and the form of the treatment (e.g., the amount of exercises, a wish for additional phone calls, or a preference for reading texts or practical exercises). Subsequently, the patient will work on the homework assignments for 3 to 4 months.

#### Characteristics E-HELD intervention

The E-HELD intervention includes modules on coping with fatigue, itch, pain, physical disabilities, negative mood, social relations, and lifestyle. In consultation between patient and e-Coach, one or two modules will be chosen based on the screening results and patient’s priorities. Consequently, every patient’s treatment has a unique character, especially since within each module different exercises can be chosen. Exercises include several homework assignments such as reading psychoeducational texts and completing personal assignments (e.g., keeping a diary of daily activities) and exercises (e.g., relaxation). Using a message box in the online environment, the e-Coach will provide weekly personalized feedback on the exercises and send motivational messages. The patient can respond to the e-Coach’s messages or ask questions via the same message box. After 3 to 4 months, the e-Coach will contact the patient for an end-of-treatment consultation to end treatment with a final module on setting long-term goals and preventing relapse.

All modules consist of evidence-based cognitive-behavioral techniques that target risk and resilience factors and were developed from standardized CBT protocols of patients with various chronic somatic conditions [68–70]. Studies on psoriasis and rheumatoid arthritis using this intervention showed promising effects on improved physical functioning and a reduced impact of disease on daily life [70, 71]. For the current study, we tailored the intervention to the needs of dialysis patients based on the results of a previous study on patient priorities [15]. Additionally, we adjusted the itch module making it suitable for dialysis patients and added lifestyle modules to support patients in adherence to medication, physical exercise, diet restrictions, and to quit smoking. For more information on the development of the intervention for the CKD and dialysis population, please see the development and treatment protocol [67].

### Criteria for discontinuing or modifying allocated interventions {11b}

When a patient’s health significantly worsens over the course of the study, the e-Coach will discuss together with the patient to either discontinue treatment, set the treatment on hold with the possibility to continue in the future, or continue treatment in an adjusted manner (e.g., lower the amount of assignments).

### Strategies to improve adherence to interventions {11c}

We will regularly ask patients to their needs and wishes in order to optimize the feasibility and the tailored character of the treatment, making the treatment personally relevant for patients. To track adherence, the e-Coach will monitor completed assignments, modules, and the amount of chat messages.

### Relevant concomitant care permitted or prohibited during the trial {11d}

Not applicable. Usual care will be continued during the course of the trial.

### Provisions for post-trial care {30}

This study does not provide post-trial care.

### Outcomes {12}

At baseline, information on socio-demographic and clinical characteristics (age, sex, education level, employment and marital status, dialysis type and duration, comorbidity, and current or previous psychological treatment) will be collected. The Charlson Comorbidity Index [72]—a measure for comorbid conditions with weighted scores for the condition—will be calculated based on patients’ medical records. In addition, we will assess computer and Internet use and treatment expectancies regarding the ICBT treatment by means of self-report. For extended information on the study outcomes and the assessment moments, see Table 1.

#### Primary outcome: distress

The primary outcome is distress, as measured by a combination of anxiety and depression using the Patient Health Questionnaire Anxiety and Depression Scale (PHQ-ADS) [45]. The 16-item PHQ-ADS combines the PHQ-9 [64] and the GAD-7 [65] as a composite measure of depression and anxiety. Higher scores indicate higher levels of depression and anxiety symptoms. Distress will be assessed at baseline, 6 months follow-up (i.e., post-treatment for the intervention group), and 12 months follow-up (i.e., 6 months post-treatment for the intervention group).

#### Secondary outcomes

All secondary outcomes will be assessed at baseline, 6 months follow-up, and 12 months follow-up (Table 1).

#### Personalized outcome assessment

The Personalized Priority and Progress Questionnaire (PPPQ) [46] is a personalized instrument to identify, prioritize, and monitor individual problems over time. The baseline measurement consists of 8 items on several domains of functioning that have proven relevant for dialysis patients in a previous study in the Netherlands, including physical health (e.g., fatigue, pain, itch), mental health (e.g., anxiety, depression), social functioning (e.g., dependence on others), and daily activities (e.g., work, hobbies) [15]. In addition, the PPPQ includes 1 item on priorities: patients are asked to select the domains they prioritize for improvement by making a top 3. The follow-up measurement assesses the amount of progress in the areas of functioning over the past 6 months (8 items). Additionally, patients indicate on which of these areas they actively worked in the previous months (1 item). Higher scores on the follow-up measurement indicate improved functioning.

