**Secondary outcomes**						
Personalized outcome assessment	Patient Priority and Progress Questionnaire (PPPQ) [46]	Patient priorities and personal meaningful changes over time. Measured by 1 item on priorities and 8 items on functioning using 5-point Likert scales for the baseline measurement and 7-point Likert scales for the follow-up measurement. Based on the follow-up measurement, a progress score is calculated on the selected priority.	−3–3, progress score, higher scores indicate subjective improvement on the selected priority as compared to the baseline measurement.	X	X	X
Domains of functioning	RAND Short Form-36 Health Status Inventory (RAND SF-36) [47]	Health-related quality of life, including physical and mental component scores. Measured by 36 items using several Likert scales and yes/no questions.	*T*-scores, *M*=50±10 in the general population.	X	X	X
	Dialysis Symptom Index (DSI) [48]	Physical and emotional symptom burden in dialysis patients. 30 items regarding the presence of symptoms, when present symptom severity is assessed by 5-point Likert scales.	30 yes/no questions, if “yes” 1=not at all, 5=very much. Minimum score is 0 when none of the symptoms are reported. Maximum score is 150 when all 30 symptoms are reported and rated as “bothers very much” (Likert scale score 5).	X	X	X
	Subjective experience of fatigue subscale, Checklist Individual Strength (CIS) [49]	Fatigue. Measured by 8 items using 7-point Likert scales.	8–56, higher scores indicate more fatigue.	X	X	X
	Itch subscale of the Impact of Chronic Skin Disease on Daily Life (ISDL) [50]	Itch. Measured by 4 items including 3 items using 4-point Likert scales and 1 VAS (0 = no itch, 10 = worst itch ever).	4–16, the 11-point VAS will be transformed into a 4-point Likert scale to assess the total score. Higher scores indicate more itch.	X	X	X
	Inventory for Social Resilience (ISR) [51]	Social functioning. Measured by the subscales perceived support (5 items), actual support (3 items), and mutual visits (2 items) using 4-point Likert scales.	5–20, perceived support. 2–13, actual support. 2–8, mutual visits. Higher scores indicate better social functioning.	X	X	X

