## Statistical methods

### Statistical methods for primary and secondary outcomes {20a}

Descriptive statistics (means, standard deviations, medians, and interquartile ranges) of relevant variables will be calculated. In case of non-normally distributed variables, transformations will be applied to allow parametric statistics. Baseline data of the intervention and control condition will be compared to assess similarity. Additionally, several *t*-tests will be performed on the 6-month follow-up data, both on the primary and secondary outcomes.

To examine differences in the primary outcome measure change in distress between patients in the intervention and control condition, a linear mixed-model analysis of variance will be conducted. Linear mixed-effects modeling has superior qualities with regard to missing values and makes use of all available data, making this a full-intention-to-treat analysis. Models will be fitted with full information maximum likelihood estimation. Between-group effects at post-treatment and follow-up will be analyzed with baseline scores of dependent variables as covariates. Time will be operationalized as a continuous variable, because post-treatment assessment will vary across participants as a result of different intervention length. Fixed linear effects of time and condition will be included and random effects of intercept.

Similar mixed-model analyses of variance will be conducted to examine differences in change in the scores on the secondary outcome measurements between the two conditions. In addition, correlational and regression analyses will be performed to assess the potential role of demographic and clinical characteristics and psychological parameters (e.g., treatment expectancies, therapeutic relationship) on the effects of the ICBT intervention.

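### The PPPQ progress score has two reference points that conflict at 12 months; if the six-month window is the real one, a fully kept benefit would score about 0

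*Protocol article*

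**What the plan says.** The PPPQ is included because the intervention is tailored to each patient (Protocol article, Objectives {7}). Its follow-up score is described in two places:

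- **Personalized outcome assessment:** "The follow-up measurement assesses the amount of progress in the areas of functioning over the past 6 months".
- **Table 1:** the form uses "7-point Likert scales for the follow-up measurement". "Based on the follow-up measurement, a progress score is calculated on the selected priority". The range is −3 to 3, and "higher scores indicate subjective improvement on the selected priority as compared to the baseline measurement".

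On timing, the Secondary outcomes section says "All secondary outcomes will be assessed at baseline, 6 months follow-up, and 12 months follow-up". The section on the primary outcome places the last visit at "12 months follow-up (i.e., 6 months post-treatment for the intervention group". Trial design {8} gives 3–4 months of treatment.

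On analysis, Statistical methods {20a} says "Similar mixed-model analyses of variance will be conducted to examine differences in change in the scores on the secondary outcome measurements". The model described there treats time as continuous, has fixed linear effects of time and condition, and has a random intercept. No time-by-condition term is listed. The same section also plans t-tests of the 6-month data for primary and secondary outcomes. Plans for assessment {18a} makes 6 months the main assessment.

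**The concern.** At the 6-month visit, a six-month look-back and a comparison with baseline cover the same interval. At the 12-month visit they do not: the look-back starts at month 6, after treatment has ended. One score cannot then be both progress over the preceding half-year and improvement since baseline. The article gives no other window for 12 months and no separate interpretation of the 12-month score.

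What is at stake is the reading of the outcome chosen to capture the personalised effect. If the window is six months and the result is read as Table 1 says, a sustained benefit could be reported as absent and a partly sustained one as deterioration. A model that estimates one condition effect across both visits would also blend two different intervals.

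**Working it through.** The plan gives no figure on this point to reproduce, so the check compares the two definitions visit by visit.

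**Inputs.** Visits at 0, 6 and 12 months (Secondary outcomes; Table 1). Treatment of 3–4 months (Trial design {8}), which falls inside the first six months. Score range −3 to 3, calculated from the follow-up form alone (Table 1).

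**Assumptions, not stated in the article.** 0 means no change (suggested by the symmetric range). Patients answer for the stated window. Changes are additive.

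**Formulas.** Let S0, S6 and S12 be a patient's state on the scored domain.

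- 6-month score, either definition: S6 − S0.
- 12-month score, six-month window: S12 − S6.
- 12-month score, against baseline: S12 − S0.

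**Illustrative courses (S0 = 0).**

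| Course | S6, S12 | 6-month score | 12-month, six-month window | 12-month, against baseline |
|---|---|---|---|---|
| Gain of 2, fully kept | 2, 2 | +2 | 0 | +2 |
| Gain of 2, half lost | 2, 1 | +2 | −1 | +1 |
| Gain of 2, all lost | 2, 0 | +2 | −2 | 0 |
| No change, then gain of 2 | 0, 2 | 0 | +2 | +2 |
| Never changed | 0, 0 | 0 | 0 | 0 |

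The 6-month score is the same under both definitions in every row. At 12 months, under the six-month window, the patient who kept the whole gain scores the same as the patient who never changed. The patient who kept half scores below zero while still better than at baseline.

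**Between arms.** Let D6 and D12 be the differences in mean state between arms, with no difference at baseline. Under the six-month window the 12-month contrast is D12 − D6. It is 0 when the difference is fully maintained, which also requires that any change in the control arm after month 6 is matched in the intervention arm.

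**Pooling.** With both visits complete and equally weighted, a single condition effect is [D6 + (D12 − D6)] / 2 = D12 / 2. For D6 = D12 = 2 this is (2 + 0) / 2 = 1, half of the difference in change since baseline.

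**The case against.** The strongest reply is that the item itself is not shown. It sits in a cited source, and a journal article may paraphrase it loosely. A reader might infer that the 12-month PPPQ result will show the effect vanishing. The documents do not support that: it follows only if the six-month window is the true 12-month wording. If Table 1 is right, the score is sound and only a sentence needs correcting. The +2 then 0 course is an illustration, not an estimate of bias.

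Two further readings are tempting and should not be pressed:

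- **Which priority is scored.** At baseline "patients are asked to select the domains they prioritize for improvement by making a top 3", whereas Table 1 scores one selected priority. This is not a contradiction, since a top 3 contains a first choice. Which one is scored is detail that the instrument's source or the analysis plan may give. The ranking is collected at baseline and screening, before randomisation.
- **No baseline value for the covariate.** The progress score has none, but the plan promises similar models, not identical ones. The baseline form rates functioning in the PPPQ domains and could supply a covariate. Naming it can be left to the analysis plan.

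The scope is also narrow. The plan already has a 6-month comparison of secondary outcomes, where the two definitions coincide. Sustained benefit can also be seen in the PHQ-ADS and in functioning scales such as the SF-36, DSI and CIS, which are scored afresh at 12 months. Finally, Statistical methods {20a} speaks of between-group effects at both post-treatment and follow-up, so visit-specific estimates may be intended.

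What stands is that the two descriptions conflict at 12 months without being reconciled, and that the fixed terms listed would not deliver visit-specific effects.

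**Conclusion.** The point holds as a conflict between two descriptions of one secondary outcome at the later of its two follow-up visits. It should be reconciled before the PPPQ is analysed.

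The wording conflict is certain; the consequence is conditional. If the administered item looks back six months, the 12-month score measures change after month 6. A benefit gained on treatment and fully kept would score about 0 and be misread under Table 1, and a single pooled condition effect would show about half of it. These sizes rest on 0 meaning no change, additive ratings and patients answering for the stated window; the pooled figure also needs equal weight on the two visits.

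The primary PHQ-ADS analysis and the 6-month PPPQ comparison are not touched.

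**What to change.** 1. Compare both descriptions with the item actually administered at 12 months, and correct whichever is wrong. If the item refers to baseline, amend the sentence in the PPPQ section; the misreading described here then does not arise.
2. If the window is six months:
   - label the 12-month PPPQ score as change from month 6 to month 12;
   - estimate the between-group PPPQ effect separately at each visit, not as one pooled condition effect;
   - make the 6-month score the main PPPQ comparison;
   - state in advance that a null 12-month score is not evidence that the effect was lost.
3. Treat any sum of the 6- and 12-month scores as exploratory. It assumes additivity, needs both visits to be complete, and runs from −6 to 6, not over Table 1's range.

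Rewording the item for visits still to come is not advised. Recruitment began in February 2019 (Trial status), so early and late participants could answer different questions.

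The cost is a few sentences in the protocol or analysis plan and slightly less information from the 12-month PPPQ. No extra data collection is needed.

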#### Domains of functioning

##### Health-related quality of life

The RAND Short Form-36 Health Status Inventory (RAND SF-36) [47] will be used to measure health-related quality of life (HRQOL). The RAND SF-36 contains 36 items that can be summarized into two summary scales: the physical component score (PCS) and the mental component score (MCS). PCS consists of the subscales physical functioning, role limitations due to physical problems, pain, and general health. MCS includes the subscales emotional wellbeing, role limitations due to emotional problems, social functioning, and vitality. Higher scores indicate a better HRQOL. The Hays norm-based scoring algorithm will be applied to transform raw scores into *T*-scores (M = 50 ± 10 in the general population) [47].

##### Symptom burden

The Dialysis Symptom Index (DSI) [48] assesses physical and emotional symptom burden in patients receiving dialysis. The DSI includes 30 items on the presence of symptoms. When present, symptom severity is rated on a 5-point Likert scale. Higher scores indicate higher symptom severity.

##### Fatigue

The subjctive experience of fatigue subscale of the Checklist Individual Strength (CIS) [49] will be used to assess fatigue. This subscale contains 8 items, with higher scores indicating more fatigue.

##### Itch

The itch subscale of the Impact of Chronic Skin Disease on Daily Life (ISDL) [50] will be used to assess itch. This subscale contains 4 items including an 11-point VAS (0 = no itch, 10 = worst itch ever). Higher scores indicate more itch.

##### Social functioning

Social functioning will be assessed by the subscales perceived support (5 items), actual support (3 items), and mutual visits (2 items) of the Inventory for Social Resilience [51]. Higher scores indicate better social functioning.

##### Lifestyle behavior

Relevant lifestyle behaviors for dialysis patients will be assessed using 8 self-constructed items. Items on diet, fluid restrictions, medication adherence, and exercise are answered on a 4-point Likert scale (1 = always, 4 = never). An example item is “I take my medication as prescribed.” Smoking behavior and weight are examined by yes/no questions (“I smoke,” “I have a healthy weight”). In addition, patients note their height and weight for BMI calculations.

### Other outcomes

All other outcomes will be assessed at baseline, 6 months follow-up, and 12 months follow-up (Table 1).

#### Psychological parameters

##### Self-efficacy

Self-efficacy will be measured by the Self-Efficacy for Managing Chronic Disease 6-ltem Scale (SEMCD-6) [52]. Higher scores indicate better self-efficacy.

##### Self-management

The Partners in Health Scale (PiH) [53] assesses chronic condition self-management knowledge and behaviors. The version of the PiH used in the study is adjusted to CKD and consists of 13 items. In this version, the illness is referred to as “kidney disease” and includes an additional item on dealing with the emotional consequences of having a kidney disease. Higher scores indicate better self-management.

